## Abstract

**Introduction:**

Mental health difficulties are a common complication affecting 1 in 5 women during the perinatal period (from conception up to two years after childbirth). As well as affecting the wellbeing of the mother, perinatal mental health difficulties can contribute to adverse long-term outcomes for the infant by disrupting the mother-infant relationship. Effective interventions are needed to enhance maternal and infant wellbeing during the perinatal period. Perinatal compassion focused therapy (P-CFT) is a promising intervention that has been adapted for perinatal mental health difficulties, and which may also help enhance the mother-infant relationship through its focus on generating compassionate and empathic cognitions of self and others. While CFT is in use in perinatal clinical settings, few studies exist that explore its potential benefits. The aims of this study were to explore the feasibility of recruitment, to determine the suitability of the outcome measures, to assess the acceptability of P-CFT through qualitative evaluation, and to explore the effects of P-CFT on compassion-based outcomes, wellbeing, and parent-infant interactions.

**Methods:**

The multisite feasibility and acceptability study will adopt a single pre-post, quasi-experimental study design comprising three components using a sample of service users attending P-CFT groups. Component 1 is a feasibility study measuring maternal self-report questionnaire outcomes (e.g., self-compassion, postpartum bonding) at baseline, post-intervention and six-month follow-up, and recruitment and retention rates. Component 2 will evaluate mother-infant interactions through the coding of video observations from baseline to post-intervention. Component 3 will entail qualitative semi-structured interviews to explore the acceptability of the intervention. Data will be analysed using statistical methods of analysis for quantitative data (Component 1 and Component 2) and reflexive thematic analysis for qualitative data (Component 3).

**Discussion:**

To the authors’ knowledge, this study will be the first multisite feasibility and acceptability study of perinatal compassion focused therapy offered to mothers and birthing parents in specialist perinatal mental health services in England’s National Health Service (NHS). This study will identify any necessary refinements for future studies and considerations for good practice in this specific population and clinical setting, as well as the intervention itself.

## Introduction

Perinatal mental health (PMH) difficulties (mental disorders occurring during pregnancy or in the two years after childbirth) are the most prevalent complications of the childbearing period, experienced by approximately 10-20% of women (1) Thus, PMH difficulties constitute a serious public health issue. In women, PMH disorders are associated with distressing symptoms, poor functioning, increased morbidity and they are a leading cause of maternal death (2–4). PMH difficulties are also linked to obstetric pregnancy complications (e.g., low birthweight, pre-term birth) as well as poorer long-term outcomes for children in terms of their cognitive, social and emotional development (2, 5–7). Given the perinatal period is a critical time for maternal and infant mental health, and the long-term health of both, it is important to find ways of supporting and improving their well-being in the perinatal phase.

The National Institute for Health and Care Excellence (8) guidelines advocate for psychological interventions for PMH difficulties to address the mother-infant relationship. However, it is unclear if and/or how the current NICE-recommended interventions for perinatal women (cognitive behavioural therapy/CBT; interpersonal therapy/IPT) can improve the dyadic relationship (9). In England and Wales, perinatal mental health community teams (P-CMHTs) offer alternative psychological interventions that appear to be beneficial in improving both PMH difficulties and the parent-infant relationship (8).

Given the challenges of pregnancy and post-partum life, psychotherapeutic interventions such as compassion focused therapy (CFT) that incorporate self-compassion may be of particular benefit to a mother’s well-being and the parent-infant relationship (10, 11). The therapy can be delivered to service users in either a group or an individual format. According to Cree (10), high levels of self-criticism and associated low levels of self-compassion are common in mothers experiencing mental health problems, and these difficulties are associated with low wellbeing, problems in perceived bonding, and the parent-infant relationship (12). Underpinned by several psychological approaches (e.g., social, evolutionary, neuroscience), Gilbert’s (13, 14) compassion focused therapy (CFT) facilitates self-compassion in individuals using psychoeducation (e.g., imbalance of the emotional regulatory systems) and experiential compassion-focused exercises (e.g., compassionate voice, compassion letter writing). Reviews of CFT and related mindfulness-based interventions indicated that CFT led to generally positive outcomes in relation to self-compassion and mental health in clinical and non-clinical samples (15–19).

In our systematic review and meta-analysis of 15 randomised studies on people experiencing mental health difficulties, interventions based on Gilbert’s (13, 14) CFT model (primarily group therapy) was associated with significant improvements in compassion-based outcomes, such as levels of self-compassion and self-reassurance and clinical symptomology (e.g., depression, disordered eating (18). Furthermore, high levels of acceptability of group CFT to service users across various clinical groups were reported in a review and meta-synthesis of 12 studies of Gilbert’s (13, 14) model of CFT (20).

Based on Gilbert’s model of CFT, Michelle Cree (11) developed an adaptation in the context of parent-infant interactions called *Perinatal Compassion Focused Therapy* (P-CFT). This adaptation aims to promote the formation of a secure attachment between mother and infant (10). It addresses how the emotional systems can be affected during pregnancy, helping mothers to understand the exacerbation of shame and self-criticism during this period as well as emotional distress in general. This adaptation of P-CFT is currently being delivered in National Health Service (NHS) perinatal services in England. However, the evidence of its effectiveness is unclear. Exploring the current evidence of Gilbert’s CFT (13, 14) and Cree’s P-CFT (10, 11) for mothers in the perinatal period, Millard and Wittkowski’s (21) review identified and reported on five studies that provided insight into the intervention’s effectiveness for PMH difficulties (22–26). Millard and Wittkowski (21) noted that significant improvements were observed in compassion-based outcomes (i.e., self-compassion, self-criticism/self-reassurance) from pre- to post P-CFT intervention. However, four of these studies (22–25) included mothers from non-clinical populations only. Therefore, the current evidence base is applicable only to perinatal mothers presenting with sub-clinical symptoms (21).

Since Millard and Wittkowski’s (21) review, another two evaluations of P-CFT groups in P-CMHTs were published: in both evaluations, service users experienced more moderate to severe PMH difficulties (27, 28). Service users presenting with a wide range of mental health difficulties were included, such as anxiety, posttraumatic stress disorder (PTSD), complex PTSD or birth trauma, obsessive compulsive disorder (OCD), personality disorders, and eating disorders. Both evaluations reported significant improvements across compassion-based outcomes, mood, and postpartum bonding, but no control groups were implemented. Although these two evaluations provided an insight into the potential benefits of P-CFT, the data were extracted retrospectively from self-reported outcomes in electronic health records. It is unclear from these evaluations if a further exploration into P-CFT is feasible in an NHS perinatal service. Given the limitations of the above-mentioned studies, a study using a stronger methodological rigour is required to explore the potential benefits of P-CFT. However, prior to a large-scale efficacy study, further exploratory studies are warranted (29). This multisite study aims to explore the feasibility and acceptability of the P-CFT groups based on Cree (10, 11) and the study design in perinatal mothers and birthing parents through three components. More specifically, the objectives are as follows:

to explore the feasibility of the study design through recruitment and retention rates and quality of data collection (Component 1, Component 2),to determine the suitability of the outcomes and their respective measures (Component 1),to assess the acceptability of the intervention through a qualitative process evaluation to identify factors associated with engagement and adherence to P-CFT (Component 3),to conduct an exploration of P-CFT has on compassion-based outcomes (i.e., self-compassion, self-criticism), psychological well-being and parent-infant interactions (Component 1, Component 2, Component 3).

## Methods

### Trial status

Recruitment started in November 2023 and is ongoing until approximately March 2026.

### Design

The study will adopt a single pre-post, quasi-experimental study design comprising three components (in this protocol, these components are referred to as Component 1, 2 and 3). This study design provides a convergent-parallel mixed methods process evaluation (30), which encapsulates the assessment of feasibility and acceptability, required as part of the MRC *Framework for Developing and Evaluating Complex Interventions* (29). The convergent-parallel approach entails the collection and analysis of quantitative and qualitative data, which are subsequently integrated and compared to allow for a unified analysis (30). Data from Components 1 and 2 will use quantitative methods and Component 3 will generate qualitative data. **Figure 1** displays an overview of the study design that reflects CONSORT guidelines (31), wherein a schedule of the study enrolment and assessments are provided in **Table 1**.

**Figure 1 f1:**
[figure not shown]
CONSORT diagram showing study design.

**Table 1 T1:** Overview of recruitment and assessment timeframes.

Study Elements			Study period			
Component	Time point	Enrolment	Time 1 (Baseline)	Intervention (Week 1 to 10/12)	Time 2 (Post-intervention)	Time 3 (Follow-up)
Enrolment						
1, 2, 3	Eligibility screening	X				
1, 2, 3	Consent to contact	X				
1, 3	Informed consent		X		X	
Intervention						
1, 2, 3	P-CFT			X		
Assessments						
1	Demographic Questionnaire		X			
1	Fear of Self-Compassion Scale (FOSC) (32)		X		X	X
1	Sussex-Oxford Compassion for Self (SOCS) (33)		X		X	X
1	Postpartum Bonding Questionnaire (PBQ) (34)		X		X	X
1	Clinical Outcomes in Routine Evaluation (CORE-10) (35)		X		X	X
1	Depression, Anxiety, and Stress Scale-21 (DASS-21) (36)		X		X	X
1	The Short Warwick-Edinburgh Mental Well-Being Scale (SWEMWBS) (37)		X		X	X
2	Parent-infant video interaction		X		X	
3	Semi-structured interviews with up to 12–14 participants				X	

As part of Patient and Public Involvement and Engagement (PPIE), two groups from two of the study research sites were consulted on the project and design of the research. Points made by the PPIE groups were considered and incorporated into the study protocol and participant documents. Throughout the study, the PPIE group will be consulted as required, such as on dissemination processes.

### Setting

The feasibility and acceptability study will be conducted in NHS specialist perinatal community mental health teams (CMHT) that are offering group P-CFT as an intervention across three NHS trusts located in the northwest, southeast, and southwest of England. In England and Wales, specialist perinatal CMHTs offer multidisciplinary support to mothers, birthing parents, and their families who are experiencing moderate to severe mental health difficulties during pregnancy and at postpartum (8). Furthermore, they can offer treatment to mothers deemed at high-risk of postpartum relapse due to their histories of moderate and severe mental health conditions. This support includes psychological therapies, psychotropic medication, and parent-infant bonding support (8).

### Intervention and its delivery

The intervention is reported in line with the Template for Intervention Description and Replication (TIDieR) checklist (38), (see **Appendix A** in **Supplementary Materials** for further details). The group P-CFT intervention is based on Cree’s (11) adaptation of Gilbert’s (13, 14) CFT (see **Appendix B** for an overview of a P-CFT course). Whilst Cree’s (11) guidance is based on 12 sessions, the number of sessions can vary between services. In this study, the P-CFT intervention will range from eight to 12 sessions, which are to be delivered remotely via online video call platform Microsoft Teams (39) or in-person at a site of the perinatal CMHT. The two-hour sessions are offered once a week in consecutive weeks. There are two group facilitators in each group, and the number of participants can range from four to eight.

### Training and adherence to protocol checks

Of the two therapy facilitators in each P-CFT group, at least one of the facilitators will have received accredited training in the CFT and/or P-CFT model. Typically, the groups are run by two facilitators, who adhere to the CFT/P-CFT model and session content as outlined in their service P-CFT therapy manual, based on the core contents as listed in Cree’s (11) P-CFT adaptation (for further details see **Appendix B**). All group facilitators will be sent the study protocol and will attend a meeting with the lead researcher ([name]). This meeting will enable the facilitators to familiarise themselves with the study protocol. The lead researcher will be in regular contact with each of the research sites throughout the recruitment stage via phone and/or email communication to ensure protocol adherence.

### Component 1: feasibility study

#### Design

This component will use a non-randomised longitudinal, repeated measures design, across three research sites through routinely collected data and self-report outcome measures.

#### Participant inclusion/exclusion criteria

Mothers and birthing parents are first referred to and assessed by the P-CMHT to determine their suitability for the service. If they meet the service criteria, they can be referred to the P-CFT group. Once enrolled to receive P-CFT and consent-to-contact is provided, the research team will assess a service user’s eligibility against the study criteria. To participate in the study, it is required that mothers^1^ are at least 18 years of age and have a baby that is less than two years old at the time of starting the P-CFT group OR they are currently pregnant and can complete the intervention prior to approximately 34 weeks gestation. Participants are excluded from the study if they are not receiving care from a P-CMHT, deemed unsuitable by the P-CMHT to receive a group intervention, assessed as acutely at risk of harm to their baby, experiencing acute psychotic symptoms, alcohol or substance misuse, active suicidality and/or lacking capacity to consent under the Mental Capacity Act 2005 (41).

#### Recruitment and consent procedures

A member of the P-CMHT will identify potential eligible participants via case note review or in a multidisciplinary meeting. The member of the P-CMHT’s psychology team will then assess if they are suitable for the P-CFT group and if they can provide consent-to-contact regarding the study. If suitable, they will be sent a study leaflet and a copy of the participant information sheet from the lead researcher ([name]). Eligible service users have at least 24 hours to think about if they would like to take part. After 24 hours, the lead researcher will conduct a phone call with the potential participant. If the individual is happy to take part, they will be asked to provide their informed consent. All online forms will be hosted via Qualtrics (42). When providing informed consent, participants can also consent to Component 2 of this study concurrently, and opt-in to being contacted about Component 3. For Component 1, participants will complete a set of demographic questions, and six outcome measures (see **Table 1** for details). To reimburse and thank them for their time and contributions, participants can consent to being entered into a prize draw (ranging from a £25-£100 gift voucher) which will be conducted at the end of the study.

Study safety procedures will be outlined to participants as part of informed consent. Active monitoring of adverse events (AEs) will be conducted throughout the study with study participants and their clinical team. We will report any severe adverse events in a future publication reporting on outcomes.

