#### Sample size consideration

Due to this study being a feasibility and acceptability study, formal sample size calculations were not undertaken. During the 28-month recruitment period of this study (from November 2023 to March 2026), it is estimated that approximately 17 groups will be offered across three NHS trusts (with ideally 4–8 participants in each group). Therefore, the potential pool of participants is 64 to 128 participants. It is planned to recruit 50% of this potential pool of participants (*n* = 32), approximately ten to 11 participants per site for baseline recruitment. This sample size reflects the median target baseline recruitment rate of 30 participants for feasibility studies in the United Kingdom (UK) (43). As an important part of the overall study aims to assess the feasibility of recruitment and retention, possible dropouts have not been factored into this calculation.

Retention of participants in the study will be examined using Lewis et al.’s (44) framework for assessing retention as a progression criterion. By applying the ‘traffic light system’, a retention rate above 85% will be considered acceptable (GREEN), 65% to 84% will be considered a borderline level of retention (AMBER), and below 65% (RED) will be deemed as a low level of retention. For any future studies on P-CFT in NHS perinatal services, a GREEN retention rate will indicate that the current study methodology is feasible for participant recruitment. Several amendments may be required to the methodology following an AMBER retention rate. A retention rate of RED demonstrates that considerable changes would be necessary to improve retention of participant recruitment. A preliminary exploration of attrition bias will also be conducted to examine if certain demographics or variables may influence attrition (e.g., number of children, financial situation).

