#### Data analysis of primary outcomes

The focus will be on tabulated and associated graphical summaries of the key indicators associated with the outcomes of a feasibility trial, which includes participant recruitment and attendance. Specifically, summary statistics will be the total number of referrals to the P-CFT groups, the number of service users who provide consent-to-contact and the number of service-users who provide their informed consent. Furthermore, group attendance and dropout rates, completion of follow-up outcome data and the number of participants who are retained at each timepoint will also be generated.

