In particular, the feasibility of the online implementation of the MACI, the parent-infant video interactions can be evaluated. In previous studies, the data collection of this tool has primarily been conducted in-person with the participants (60). However, this method was not feasible for this study due to the locations of the recruitment sites. As recruitment is being delivered online, some novel aspects require evaluation for feasibility. Srikar et al. (59) reported that an online/remote version of the MACI-Infant measure was feasible to use in mothers with infants at elevated likelihood of autism. Nevertheless, it is unclear if an online/remote delivery of the MACI-Infant is feasible among mothers with perinatal mental health difficulties. From a practical perspective, this current study will look at aspects such as whether or not the interaction can be sufficiently set up remotely by participants, whether the self-recordings can be correctly recorded and sent to the researchers through their home devices and the suitability of recording through teleconferencing software, and generally, whether this method is acceptable among the group of mothers and birthing parents. As Component 2 is an optional aspect of the study, the recruitment rate will be able to indicate the willingness of participants to take part in a caregiver-infant interaction study. A meta-synthesis of parental experiences of video feedback parenting interventions highlighted that participating in recorded video interactions can often elicit feelings of self-doubt and anxiety (71). The implementation of remote data collection may help to mitigate this potential issue.

It is important to identify the appropriate outcome measures for perinatal mothers and birthing parents experiencing mental health difficulties. Some of the outcome measures and/or their specific items may elicit distress in participants. By allowing the participants to skip items that they may not be comfortable in answering, the study can determine which specific items or questionnaires are acceptable in this population.

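### Adverse events are monitored without a grade limit, but the article commits to publishing only an undefined severe subset, so publication of other events is not assured

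*Protocol article*

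**What the plan says.** Adverse events are dealt with in one place in the protocol article: the end of *Recruitment and consent procedures* under Component 1. Three consecutive sentences cover them.

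- Safety procedures: "Study safety procedures will be outlined to participants as part of informed consent". The procedures themselves are not set out in the article.
- Collection: "Active monitoring of adverse events (AEs) will be conducted throughout the study with study participants and their clinical team". No grade or type of event is excluded.
- Publication: "We will report any severe adverse events in a future publication reporting on outcomes". The word *severe* is not defined, and *serious* is not used of adverse events anywhere in the article.

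The analysis sections add nothing on adverse events. *Data analysis of primary outcomes* covers referrals, consent to contact and informed consent, and then says that "group attendance and dropout rates, completion of follow-up outcome data and the number of participants who are retained at each timepoint will also be generated". The matching section for the secondary outcomes covers the questionnaire scores, effect sizes and individual reliable change.

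The *Discussion* anticipates harm of a lesser kind: "Some of the outcome measures and/or their specific items may elicit distress in participants". It also cites a meta-synthesis of video feedback interventions in which being recorded was linked to self-doubt and anxiety.

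**The concern.** The article uses the general term for what is monitored and a restricted term for what is published. Two groups of events fall in the gap.

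The first is every event below severe, whether caused by the group, the questionnaires or the video recording. The second arises from the choice of word. In harms reporting, severity grades intensity and seriousness refers to consequence, such as a hospital admission. A serious event of moderate intensity lies outside the sentence if *severe* carries its usual technical meaning.

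Acceptability is a stated objective, and the results are meant to identify refinements for the intervention and for future studies. There is no control group, so a plain descriptive account of all recorded events is among the most useful safety information the study can pass on. A publication that kept to the letter of the sentence could mention no adverse events while the study held records of lesser ones.

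**Working it through.** No arithmetic applies. The article states no adverse event rate, no severity split and no safety target, and on sample size it says that "formal sample size calculations were not undertaken". The check is a comparison of the relevant statements.

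**1. Collection against publication**

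| Step | Scope in the article | Limit by grade |
|---|---|---|
| Monitoring | Adverse events, from participants and clinical teams, throughout | None |
| Publication | Severe adverse events | Severe, undefined |

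The second scope is narrower than the first.

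**2. Does another section widen the publication scope?** The primary summaries are referrals, consent, attendance, dropout, completion and retention. The secondary summaries are scores, effect sizes and reliable change. Neither includes adverse events, so the single sentence is the whole of the stated publication commitment.

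**3. Does the result depend on what *severe* means?**

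- If it grades intensity, the commitment covers neither non-severe events nor serious events graded below severe.
- If it was a loose word for *serious*, the second group is covered, but non-serious events still are not, and the word needs correcting.

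Under either reading, some monitored events have no commitment to publication.

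**4. Are events of that kind foreseeable here?** Yes, on the article's own account. It says that some measures or items may cause distress and notes possible anxiety about being recorded. Such reactions need not be severe. The article does not say how common or how intense they will be.

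**5. Would other planned results supply the same information?** Only in part.

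- *Scores and reliable change.* Worsening on the questionnaires can show here, since the planned percentage with clinically significant change is not limited to improvement. However, a score change is not a record of an event, its cause or its consequence.
- *Skipped items and completion rates.* These signal that an item is uncomfortable, but only indirectly.
- *Interviews.* The target is 12, with a range of 10 to 15. Interviewees need not have taken part in Components 1 and 2. Those identified through the sites must have completed at least 50% of a group, so that route does not reach people who left early.

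None of these replaces a count of the adverse events actually recorded.

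**The case against.** The strongest reply is that the sentence sets a minimum. It promises to report severe events and does not say that others will be excluded. The word may be a loose use of *serious*, since the article gives no intensity grading. Definitions, grading, relatedness and tabulation are commonly left to the full protocol or analysis plan, which is not shown, and the article mentions safety procedures it does not reproduce. Worsening, uncomfortable items and experience of the group are partly captured by the planned scores, completion rates and interviews. Acceptability is to be judged from interviews, attendance and completion, not from event counts.

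Much of this stands, and it limits the point. A reader might infer that non-severe events will be thrown away, that these make up the bulk of the harms data, or that a serious event of moderate intensity will certainly go unreported. The documents support none of these. The text contains no exclusion and gives no severity distribution. It concerns one future publication, not safety reporting through other channels. Nor is it shown that the acceptability conclusion would be biased.

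What the reply does not remove is that the article goes beyond silence. It states which events the outcomes publication will report, and that statement is narrower than what will be monitored. The absence of definitions or tables would be no finding by itself. The finding is a stated commitment with a limiting word that is undefined and possibly the wrong one.

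**Conclusion.** The point holds as a matter of reporting scope. All adverse events are to be monitored, the stated publication commitment reaches only those called severe, and nothing else in the article widens it. Publication of non-severe events, and of serious events not graded severe, is therefore not assured. The second part assumes that *severe* is meant as a grade of intensity; the first holds under either meaning.

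The size cannot be put as a number, because the article gives nothing from which to derive how many events fall outside the commitment. No sample size, estimate or progression threshold is affected. The change is still worth making: it is small, and it secures safety information that a larger trial would need.

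**What to change.** Replace the publication sentence with a commitment along these lines:

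> All recorded adverse events will be reported as number of events and number of participants affected, by seriousness, severity and relatedness to the P-CFT group or to study procedures. Serious adverse events will be listed individually.

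State what *serious* and *severe* each mean, or refer to the document that defines them.

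Use all consented participants as the denominator, and those who started P-CFT for events related to the group. The wider denominator is needed because baseline questionnaires and the baseline video take place up to four weeks before the first session. A participant can therefore be exposed to study procedures and never start the group.

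The cost is one descriptive table from data already collected. If seriousness, severity and relatedness are not already noted for each event, they would also have to be assigned; the article does not say whether they are. The outcomes publication is still described as future, so the change can be made before results are reported.
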